### Instructor training

Exercise classes were led by Seniors’ Fitness Instructors, certified through the Canadian Centre for Activity and Aging [59]. Members from our research team underwent an in-person training session with one of the original developers of the SSE program and study co-investigator ([name]). Our research team then developed the SSE protocol to be used as the mind-motor component within the M4 group and conducted training with all instructors on the M2 and M4 class exercise protocols, in order to ensure standardized delivery of the programs.

### Outcome assessment

Outcomes are measured at baseline, 24 weeks (intervention endpoint) and 52 weeks (study endpoint) (see Fig. 2). Measurement sessions were conducted over 2 to 3 consecutive days; training emphasizes strict adherence to all written study protocols. All participants, regardless of their compliance with the exercise intervention, are telephoned one month in advance to book appointments.

**Fig. 2 Fig2:**
[figure not shown]
Study Flow

#### Baseline data

Baseline measurements were obtained prior to randomization. In addition to the measurements described below, the following were also collected: demographic and general health characteristics; medical history and medications; anthropometric and fitness measurements; cognitive functioning using the Montreal Cognitive Assessment (MoCA) [60]; and current physical activity levels using the Phone-FITT physical activity interview [61].

#### Measurement protocols

##### Cognition

Global cognitive functioning, as well as domain-specific cognitive functioning, is calculated using the Cambridge Brain Sciences (CBS) computerized cognitive battery (www.cambridgebrainsciences.com). The CBS contains 12 non-verbal, culturally independent tests, which cover four broad cognitive domains (i.e., memory, reasoning, concentration, planning or EF) [62] (see Table 2). Six of the 12 tasks emphasize abstract reasoning, planning and problem solving, and these tasks were specifically included since they correlate highly with measures of general fluid intelligence [63]. The CBS tasks are fully automated, and have been used to effectively evaluate cognition in a several large-scale, population-based studies [46, 62]. The CBS cognitive battery is a computerized adaptive testing platform that randomly generates novel versions of the tasks between individual trials and can be administered in 60 minutes, thereby eliminating the potential to observe specific test-related practice effects or participant fatigue that are common to traditional paper-based cognitive assessments. The CBS tasks are conducted using laptop computers and a trackball mouse using authorized copies that have been obtained from one of the original developers and study co-investigator ([name]). The CBS is administered on Day 1 of each measurement session for familiarization purposes only, in order to ensure participants feel comfortable using the trackball mouse and also to prevent any learning effects [62]. On Day 2 of the measurement session, the CBS testing session occurs.

**Table 2 Tab2:** Description of Cambridge Brain Sciences cognitive battery

Task Name	Cognitive Domain	Brief Description	Outcome Measure
1. Monkey Ladder	Memory	Sets of numbered squares are displayed all at the same time at random locations within an invisible 5x5 grid. After a variable interval, the numbers are removed leaving just the blank squares visible. A tone cues the participant to respond by clicking on the squares in ascending numerical sequence.	Maximum level achieved
*(Visuospatial working memory)*			*The amount of squares presented increases or decreases by 1 after each trial depending on whether they responded correctly. The first trial contains 4 numbered squares.*
2. Grammatical Reasoning	Reasoning	Problems of the form “The square is not encapsulated by the circle” are displayed on the screen and the participant must indicate whether the statement correctly describes a pair of objects displayed in the centre of the screen.	Total score
*(Verbal Reasoning)*			*In order to achieve maximum points, the participant must solve as many problems as possible within the given time. The total score increases or decreases by 1 after each trial depending on whether they responded correctly.*
3. Double Trouble	Reasoning	A coloured word is displayed at the top of the screen (e.g., the word RED drawn in blue ink). Participants must indicate which of two coloured words at the bottom of the screen describes the colour that the word at the top of the screen is drawn in. The colour word mappings may be congruent, incongruent, or doubly incongruent, depending on whether or not the colours that a given word describes matches the colour that it is drawn in.	Total score
*(Colour-Word Remapping)*			*To gain maximum points, the participant must solve as many problems as possible within the given time. The total score increases or decreases by 1 after each trial depending on whether they responded correctly.*
4. Odd One Out	Reasoning	A 3x3 grid of cells is displayed on the screen. Each cell contains a variable number of copies of a coloured shape. The features that make up the objects in each cell (colour, shape, number of copies) are related to each other according to a set of rules. The participant must deduce the rules that relate the object features and select the one cell whose contents do not correspond to those rules.	Total correct
*(Deductive Reasoning)*			*To gain maximum points, the participant must solve as many problems as possible. If the response is correct, the total score increases by one point and the next problem is more complex. If the response is incorrect, the total score decreases by 1 point.*
5. Spatial Span Blocks	Memory	16 squares are displayed in a 4x4 grid. A subset of the squares flash in a random sequence at a rate of 1 flash every 900 ms. Subsequently, the mouse cursor is displayed and a tone cues the participant to repeat the sequence by clicking on the squares in the same order in which they flashed.	Maximum level achieved
*(Spatial Span)*			*To gain maximum points, the participant must solve as many problems as possible. If the response is correct, the number of illuminated squares increases by one. If the response is incorrect, the number of illuminated squares decreases by 1. The first trial contains 4 illuminated squares.*
6. Rotations	Concentration	In this variant, 2 grids of coloured squares are displayed to either side of the screen with 1 of the grids rotated by a multiple of 90°. When rotated, the grids are either identical or differ by the position of at least 1 square. In order to gain maximum points, the participant must indicate whether the grids are identical, solving as many problems as possible.	Total score
*(Spatial Rotations)*			*If the response is correct, the total score increases by the number of squares in the grid and subsequent trials have more squares. If the response is incorrect, the total score decreases by the number of squares in the grid and subsequent trials have fewer squares. The first grids contain 4 coloured squares each.*
7. Feature Match Task	Concentration	Two grids are displayed on the screen, each containing a set of abstract shapes. In half of the trials the grids differ by just one shape. In order to gain maximum points, the participant must indicate whether or not the grid contents are identical, solving as many problems as possible.	Total score
			*If the response is correct, the total score increases by the number of shapes in the grid and the number of shapes in subsequent trials increases. If the response is incorrect the total score decreases by the number of shapes in the grid and subsequent trials have fewer shapes. The first grids contain four abstract shapes each.*
8. Digit Span	Memory	Participants view a sequence of digits that appear on the screen one after another. Subsequently, participants are required to repeat the sequence of numbers by using the mouse cursor to click a series of numbered buttons that appear along the bottom of the screen.	Maximum level achieved
			*If the response is correct, the total length of the sequence increases by 1. If the response is incorrect, the total length of the sequence decreases by 1. The first trial contains a four-digit sequence.*
9. Hampshire Tree Task	Planning	Nine numbered beads are positioned on a tree shaped frame. The participant repositions the beads one-by-one so that they are configured in ascending numerical order running from left to right and top to bottom of the tree.	Total score
*(Spatial Planning)*			*After each trial, the total score is incremented by adding the minimum number of moves required × 2 (the number of moves actually made), thereby rewarding efficient planning.*
10. Paired Associates	Memory	Boxes are displayed at random locations on an invisible 5x5 grid. The boxes open one after another to reveal an enclosed object. Subsequently, the objects are displayed in random order in the centre of the grid and the participant must click on the boxes that contained them.	Maximum level achieved
			*If the response is correct, the total number of objects increases by 1. If the response is incorrect, the total number of objects decreases by 1, and subsequent trials have fewer objects. The first trial contains 4 objects.*
11. Polygons	Concentration	A pair of overlapping polygons is displayed on one side of the screen. In order to gain maximum points, the participant must indicate whether a polygon displayed on the other side of the screen is identical to one of the interlocking polygons, solving as many problems as possible.	Total score
*(Interlocking polygons)*			*If responses are correct, the total score increases by the difficulty level and the differences between the polygons becomes increasingly subtle.*
			*If the responses are incorrect, the total score decreases by the difficulty level and the difference between the polygons become more pronounced.*
12. Spatial Search	Planning	Sets of boxes are displayed on the screen in random locations within an invisible 5x5 grid. The participant must find a hidden “token” by clicking on the boxes one at a time to reveal their contents. When the token is found, it is hidden within another box.	Maximum level achieved
*(Self-Ordered Search)*			*If the response is correct, the total number of boxes increases by 1. If the response is incorrect, the total number of boxes decreases by 1, and subsequent trials have fewer boxes. The first trial contains 5 boxes.*

Note: All tasks are performed for a total of 5 minutes; three 90-second blocks, separated by two 15-second rest periods. During the rest periods, the neuropsychological tasks are hidden from view. Following each rest period, the task is returned to view, and participant continue from the last, correctly completed level of difficulty

Composite scores for each cognitive domain will be derived using previously published methods [64] as follows: i) calculating baseline group means and standard deviations from each task; ii) for each task, converting scores to standardized z scores (subtracting baseline group mean from raw score and dividing by baseline group SD); and then iii) within each domain, averaging task standardized scores to create domain-specific standardized scores. The four domain-specific standardized scores will then be averaged to create a global cognitive functioning score.

##### Ambulatory BP monitoring

Participants are fitted with a 24-hour ambulatory BP monitor (Model 90207, Spacelabs Inc., Redmond, WA, USA). A total of 40 readings are recorded over a 24-hour period, with one measurement obtained every half hour during the day (06:00–22:00), and once every hour during the night (22:00–06:00). Participants are instructed to relax the arm and remain still during cuff inflation and deflation; in case of measurement error, the monitor performs an automatic repeat attempt two minutes later. Participants are instructed to keep the cuff on for the entire 24-hour period and to abstain from showering or water activities. An activity log is provided to record any events that could affect BP, such as physical activity or stressful situations. A minimum of 32 measurements (80 %) will be required for statistical analysis. Systolic and diastolic ambulatory BP will be averaged for day-time hours, night-time hours, and then over the entire 24-hour period [65].

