### Statistical methods

We will analyze data based on an intent-to-treat approach, using mixed models for repeated measurements, which encompasses ANCOVA as a special case [70]. Therefore, we will include all enrolled participants in analyses and analyze data according to the randomization scheme. For our primary outcome, we will examine the difference between the M4 and M2 groups at 24 weeks in mean change of global cognitive functioning. Our secondary analysis will include examining the difference between groups at 52 weeks in mean change of global cognitive functioning. Next, we will examine differences between groups at 24 at 52 weeks on i) cognitive outcomes: memory, reasoning, concentration and EF; ii) mobility-related outcomes: usual and DT gait velocity, step length and stride time variability, and total FAB score; and iii) vascular outcomes: 24-hour systolic and diastolic BP, CAC, and carotid IMT.

For our primary outcome, we will also conduct sensitivity analyses whereby: 1) we will additionally adjust for age, sex, and baseline cardiorespiratory fitness; and 2) we will only include participants who complete a 24-week assessment and attend at least 80 % of exercise classes (i.e., “all-completers analysis”). For our primary analysis, we will also examine interactions involving age, sex, and baseline cognitive functioning (via the MoCA score). Two-sided P-values less than 0.05 will be claimed as statistically significant; however, interpretation of study results will primarily be based on estimation and associated 95 % confidence intervals [52].

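### The 32-reading rule for ambulatory blood pressure can be met with no night readings, so a record can count towards 24-hour BP without containing any night

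*Protocol article*

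**What the plan says.** In the protocol article, under Ambulatory BP monitoring:

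- Schedule: "A total of 40 readings are recorded over a 24-hour period". Readings are half-hourly from 06:00 to 22:00 "and once every hour during the night" (22:00 to 06:00). A failed reading is retried once, automatically, two minutes later.
- Validity: "A minimum of 32 measurements (80 %) will be required for statistical analysis". No separate minimum is given for day or for night.
- Derivation: systolic and diastolic pressure "will be averaged for day-time hours, night-time hours, and then over the entire 24-hour period", with a published source cited for the method. The text does not say whether the 24-hour figure is a plain mean of all valid readings or a combination of the day and night means.

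Under Statistical methods, the vascular outcomes compared between groups at 24 and 52 weeks are "24-hour systolic and diastolic BP, CAC, and carotid IMT". The separate day and night means are derived but not named there for comparison.

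**The concern.** The validity threshold equals the number of readings scheduled for the day alone. It therefore checks how many readings exist but not whether they cover the 24 hours. A record from which the whole night is missing passes; a record with a full night and 23 day readings fails.

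The outcome at stake is the only ambulatory summary named for the group comparison. If the 24-hour value is a plain mean, its content varies with the number of night readings that happen to succeed. Two visits by one participant can then differ only because the mix of day and night readings differs. The listed comparisons would not show this, because the day and night means are not among them.

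**Working it through.** **Inputs from the protocol article:** 16 daytime hours at 2 readings per hour; 8 night hours at 1 per hour; 40 readings in total; threshold 32, given as 80%. **Assumption, not in the documents:** a day-night fall F of 10 to 20 mmHg, for illustration only.

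**1. The plan's own figures.** 16 × 2 = 32 day readings; 8 × 1 = 8 night readings; 32 + 8 = 40. 32/40 = 80%. Both stated figures reproduce.

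**2. What the threshold admits.** 32 day + 0 night = 32: accepted. 23 day + 8 night = 31: rejected. With exactly 32 readings, the mix can run from 32 + 0 to 24 + 8.

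**3. Weight of the night under a plain mean.** Night weight = night readings / all valid readings.

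- Complete record: 8/40 = 20%
- 24 + 8: 8/32 = 25%
- 32 + 0: 0/32 = 0%
- Share of the clock: 8/24 = 33.3%

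**4. Size in mmHg.** Excess of the plain mean over the time-weighted mean = F × (1/3 − night weight).

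| Valid readings (day + night) | Night weight | F = 10 | F = 15 | F = 20 |
|---|---|---|---|---|
| 24 + 8 | 25% | 0.83 | 1.25 | 1.67 |
| 32 + 8 | 20% | 1.33 | 2.00 | 2.67 |
| 32 + 4 | 11.1% | 2.22 | 3.33 | 4.44 |
| 32 + 0 | 0% | 3.33 | 5.00 | 6.67 |

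The largest shift between two accepted records of one participant with unchanged pressure is F × (0.25 − 0) = 2.5, 3.75 or 5.0 mmHg.

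**5. Effect on the M4-M2 difference, complete records in both arms.** Plain mean: 0.8 × day effect + 0.2 × night effect. Time-weighted: (2 × day effect + night effect)/3.

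- Day −3, night −3: −3.0 either way
- Day −3, night 0: −2.4 against −2.0
- Day 0, night −3: −0.6 against −1.0

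So the weighting leaves a uniform effect intact, enlarges a daytime effect and shrinks a night-time one.

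**6. If completeness differs by arm.** The resulting error in the group difference is F × the difference in mean night weight. As an extreme example, if every participant in one arm lost half of the night readings (32 + 4) and nobody in the other did, it would be F × (0.200 − 0.111), which is 0.9 mmHg at F = 10 and 1.8 mmHg at F = 20.

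**7. The other reading of the derivation.** If the 24-hour value is formed from the day and night means, the accepted 32 + 0 record has no night mean. Neither its night value nor its 24-hour value can be computed, although the rule calls it fit for analysis.

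**The case against.** A reader might infer that the trial's 24-hour BP outcome is biased towards daytime. The documents do not support that, for two reasons.

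First, the weighting is not stated. A plain mean is the natural reading, but the sentence can also be read as combining the day and night means, and it relies on a source that is not shown. An article may leave such derivation detail to the full protocol or analysis plan, so silence on the weighting is not itself the fault.

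Second, both arms share the monitor, the schedule and the threshold. A constant over-weighting of daytime shifts the level in both arms and cancels in the comparison when day and night effects are equal. Nothing in the documents suggests that night completeness will differ by arm. The mmHg figures in step 4 are offsets in one participant's level, not errors in M4-M2, and they rest on an assumed fall.

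It is also fair to say that a record with no night readings is an extreme. Participants are told to wear the cuff throughout and failed readings are retried, which reduces night loss without excluding it. The documents give no basis for estimating how often it would occur.

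All of this limits the consequence. It does not rescue the threshold, which the document does state and which fails to protect the 24-hour value under either reading of the derivation.

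**Conclusion.** The point holds for the validity rule. It follows from the protocol's own schedule, without outside figures, that a record with no night readings is accepted for a 24-hour outcome.

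The over-weighting of daytime (80% of the weight against 66.7% of the clock on a complete record) is conditional on a plain mean of readings. Under that reading, and for an assumed fall of 10 to 20 mmHg, a participant's value can move by up to 2.5 to 5 mmHg between visits for no physiological reason. The consequences are added noise in the change from baseline and, where day and night effects differ, a different average effect from the time-weighted one. Bias in the M4-M2 difference requires night completeness to differ by arm, which is possible but not shown.

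This concerns 24-hour systolic and diastolic BP only. It is worth correcting but does not touch the primary outcome, its analysis or the sample size.

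**What to change.** 1. Define 24-hour BP as (16 × day mean + 8 × night mean)/24. Daytime then carries 66.7% however many readings succeed, provided both means exist.
2. Replace the single threshold of 32 with a minimum for each period, for example about 80% of each. For the day, 0.8 × 32 = 25.6, so 26. For the night, 0.8 × 8 = 6.4, so the cut-off must be rounded to 6 (75%) or 7 (87.5%). Choose it before unblinding. A cut-off of 7 would drop a 32 + 6 record that is 38/40 = 95% complete, and time-weighting removes much of the reason to be that strict.
3. If the night minimum is not met, treat 24-hour BP as missing in the planned mixed model and keep the record for daytime BP.

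The change needs a short edit to the derivation and uses readings already recorded. Its cost is that some records with few night readings leave the 24-hour outcome; the documents do not allow their number to be estimated. The 23 + 8 record would still fail a day minimum of 26, but then because its daytime coverage is short (23/32 = 72%).

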##### Common carotid arterial ultrasonography

Participants are instructed to avoid engaging in vigorous exercise or drink alcohol for 24 hours, avoid caffeine and smoking for 12 hours, and fast for 4 hours prior to the ultrasound measurement. Participants are instrumented with a standard three lead electrocardiogram and undergo 10 minutes of supine rest in a quiet, temperature controlled room. With the participant’s head turned approximately 45 degrees towards the left, a 10Mhz transducer is placed longitudinally along the right carotid artery, 1–2 cm proximal to the carotid sinus, to obtain two-dimensional B-mode ultrasound images (Vingmed System 5, GE Ultrasound A/S, Horton, Norway). Right common carotid arterial diameters are measured in triplicate from wall to wall, and from wall to intima media layer at end diastole and peak systole. Doppler ultrasound is used to collect pulse wave for 60 seconds. Following acquisition of the ultrasound images, carotid pulse pressure is inferred from supine brachial arterial BP (BPM-100, BPTru™ Medical Devices, Coquitlam, BC, Canada). Anatomic land marking is used to ensure that all ultrasound images are obtained from the same portions of the carotid artery and to ensure accurate comparisons over time.

Carotid arterial compliance (CAC) will be determined using the following equation: CAC = [π(D_max_/2)^2^ – π(D_min_/2)^2^]/ΔP [66], where D_max_ is the systolic carotid arterial diameter, D_min_ is the diastolic carotid arterial diameter, and ΔP is the automated supine brachial pulse pressure. Carotid intima-media thickness (IMT) will be determined by subtracting the carotid arterial lumen diameter from the arterial diameter at diastole. Two trained technicians are responsible for obtaining and analyzing all ultrasound images, with the same technician performing all assessments on a given participant whenever possible. Immediately following the ultrasound measurement, all participants are offered a standardized snack.

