### Sample size

The sample size calculation is based on the primary outcome and analysis. To our knowledge, no study to date has observed the effect of a 6-month multiple-modality and mind-motor exercise intervention on global cognitive functioning in older adults with cognitive complaints. A meta-analysis on the impact of aerobic fitness training on cognition in older adults suggested that physical exercise can improve cognition with an effect size of *d* = 0.48 [35]. Although the CBS is grounded in well-validated neuropsychological tests [46], it has not been used to date as an outcome in published exercise intervention studies. For these reasons, sample size for the proposed study must be approximated by using the effect size approach, combined with feasibility and comparisons to sample sizes used in other similar studies.

With 52 participants per group, our study would have 80 % power at the 5 % significance level to detect an effect size (mean difference divided by SD) of 0.55, a moderate effect size. We estimated a dropout rate of 20 % during the 24-week period, which increased our calculation to 65 participants per group. Thus, we proposed that 130 participants (65 participants per group) is a reasonable sample size.

The 20 % drop out rate is conservative since we observed a drop out rate of 16 % in a previous study [50]. This sample size may also be considered conservative since we will be using a variant of Analysis of Covariance (ANCOVA) to perform data analysis for the primary outcome. This proposed sample size is also in line with two exercise intervention studies for older adults with cognitive complaints; specifically, the MAX trial [37], where 126 individuals were enrolled, and a trial by Lautenschlager et al. [38], where 170 participants were enrolled.

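### The carotid IMT formula subtracts a lumen diameter that is not among the diameters listed as measured, so the text does not settle whether the result covers one wall or two

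*Protocol article*

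**What the plan says.** The Protocol article, section Common carotid arterial ultrasonography, contains two statements that bear on IMT.

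- **Acquisition.** Right common carotid diameters are "measured in triplicate from wall to wall, and from wall to intima media layer at end diastole and peak systole".
- **Derivation.** IMT "will be determined by subtracting the carotid arterial lumen diameter from the arterial diameter at diastole".

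The section does not define the lumen diameter, lists no inner-edge to inner-edge measurement, does not say which wall's intima-media layer ends the second measurement, and states no division by two.

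Under Statistical methods, IMT is one of the outcomes to be compared between groups at 24 and 52 weeks: "vascular outcomes: 24-hour systolic and diastolic BP, CAC, and carotid IMT". The same section sets a two-sided 0.05 threshold but says that results will be read mainly from estimates and 95% confidence intervals.

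**The concern.** IMT is the thickness of one wall. A diameter crosses the whole vessel, so the gap between an outer and an inner diameter holds the near wall and the far wall together. A reader who applies the derivation sentence as worded, with a true lumen diameter, obtains twice the quantity that the sentence names. A reader who takes the second diameter from the acquisition sentence may obtain the right quantity, but only by subtracting something other than what the formula names.

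The scale matters because the plan puts the weight on estimates and intervals. A doubled IMT would carry through to the reported means, the group difference and both confidence limits, and would spoil comparison with IMT values from elsewhere. The p-value would look the same either way and so would give no warning.

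**Working it through.** The plan states no numerical IMT, so there is no figure to reproduce. The check is geometric.

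**Inputs**
- From the acquisition sentence: a wall-to-wall diameter, and a wall-to-intima-media-layer diameter.
- From the derivation sentence: arterial diameter minus lumen diameter, at diastole.
- Notation: T is the thickness of one wall and L the inner-to-inner lumen. Near and far walls are assumed equal, and the wall-to-wall diameter is assumed to run between the outer boundaries.

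**Formulas**
- Wall to wall = L + 2T.
- True lumen diameter = L.
- Near wall to far-wall intima-media layer = L + T.

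**Reading A, a true lumen diameter is subtracted**
(L + 2T) - L = 2T. Dividing by 2 gives T.

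**Reading B, the second listed diameter is subtracted, ending at the far-wall layer**
(L + 2T) - (L + T) = T. No division is needed, and halving would give T/2.

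**Illustration** (all values assumed, none is in the plan; L = 6.0 mm)

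| T (mm) | Wall to wall | Reading A | A / T | Reading B | B / T |
|---|---|---|---|---|---|
| 0.6 | 7.2 | 7.2 - 6.0 = 1.2 | 2.0 | 7.2 - 6.6 = 0.6 | 1.0 |
| 0.8 | 7.6 | 7.6 - 6.0 = 1.6 | 2.0 | 7.6 - 6.8 = 0.8 | 1.0 |
| 1.0 | 8.0 | 8.0 - 6.0 = 2.0 | 2.0 | 8.0 - 7.0 = 1.0 | 1.0 |

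L cancels in both readings, so the ratios do not depend on the assumed lumen.

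**Effect on the analysis.** If every value is multiplied by 2, the group difference d becomes 2d and its standard error SE becomes 2 x SE. Then t = 2d / (2 x SE) = d / SE, unchanged. A simulated example (52 per group; assumed means 0.80 and 0.75 mm, SD 0.15 mm) gave t = 2.2227 and p = 0.0284 on both scales, while the observed difference went from 0.0558 to 0.1116 mm.

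**Reach.** The Sample size section bases its calculation on the primary outcome and analysis, so IMT does not enter it.

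**The case against.** The strongest reply is that the section should be read as a whole. It lists only two diameters, so the only one available to subtract from the wall-to-wall value is the wall-to-intima-media diameter. Reading B then applies, the result is a correct single-wall IMT, and lumen diameter is just a loose label. On this view the point is one of wording, about one secondary outcome, and the exact placement of the measurement belongs in the written study procedures, which are not shown.

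Much of this stands. Three stronger inferences that a reader might draw are not supported:

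- **That the reported IMT will be twice the true value.** This follows from the derivation sentence alone. The acquisition sentence offers a reading under which the value is right.
- **That the formula should simply be divided by two.** If Reading B describes the stored data, halving would turn a correct T into T/2.
- **That the two technicians may be working on different scales.** Nothing in the article suggests it. Both are described as trained, the same one is to assess a given participant where possible, and the Outcome assessment section stresses adherence to written procedures.

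The reply does not clear the formula, however. A diameter of L + T includes one wall and is not a lumen diameter, so Reading B rescues the result only by replacing the term that the formula uses. Nor is this a detail left to another document: the article states the rule, and the rule does not fit the measurements listed beside it.

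**Conclusion.** The concern holds as a mismatch between the stated formula and the stated measurements. On one reading the formula lacks a division by two; on the other it names a diameter that is not the one measured. The sentence needs correcting either way, and the article alone cannot say which correction is right.

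The size is a factor of 2.0 or 1.0 in the IMT values, their group difference and the confidence limits. An assumed true IMT of 0.7 mm would be reported as 1.4 mm under Reading A and as 0.7 mm under Reading B. The exact factor of 2 rests on equal near and far walls; with unequal walls, Reading A gives their sum. Reading B further assumes that the second diameter ends at the far-wall layer, which the text does not say.

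The consequence is confined to the scale of one secondary outcome. Provided that one convention is used throughout, the test and the standardised effect are unaffected, and so are the primary outcome and the sample size. It is still worth correcting, because the plan makes estimates and intervals the main basis of interpretation.

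**What to change.** 1. Establish from the measurement procedure and the stored data which second diameter was recorded.
2. If it runs from the near wall to the far-wall intima-media layer, put that measurement in the formula in place of the lumen diameter, and do not halve: IMT = wall-to-wall diameter - near-wall to far-wall intima-media diameter, at end diastole.
3. If it is a true inner-to-inner lumen diameter, correct the acquisition sentence to say so and define IMT = (wall-to-wall diameter - lumen diameter) / 2, at end diastole.
4. Before unblinding, check the stored IMT values against the chosen definition, and rescale only if they do not match it.

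The cost is one or two corrected sentences and a check of stored values, with a rescaling if needed. No new data are required.
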